### Procedure

#### Recruitment

Participants will be recruited from six primary health care centers in HK. Attendees of the center will be approached (Figure 1). Smokers will be identified through a preliminary screening. Individuals who smoke will be invited to complete a baseline questionnaire administered by a member of the clinic’s staff or by a research assistant who conducted the screening. Subjects will also be invited to perform an exhaled carbon monoxide (CO) test in the clinic at baseline. Subjects who meet the criteria for inclusion in the study following the screening and who are interested in participating in the study will be asked to provide their written informed consent.

#### Randomization

Eligible participants will be randomized to either the ACT or the control group. The randomization process will be based on computer-generated randomization numbers placed in sealed and opaque envelopes. A serial number will be given to each envelope. Each envelope will then be opened by the research assistant in sequence, according to the sequence by which the subjects were admitted at the respective center. The randomization procedure will be undertaken by another research assistant not directly involved in the study.

#### Follow-up assessments

At three and six months, the participants will be re-contacted by telephone to complete the follow-up assessments assessing their smoking status, attempts to quit, and ability to deal with physical sensations, emotions, and thoughts without smoking. The assessments will be conducted by trained research assistants who are blind to the treatment condition. Participants who self-report as quitters at the six-month follow-up interview will be invited to perform the CO test in the clinic. Participants in the ACT group will also need to complete an evaluation survey through telephone at the six-month follow up session.

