#### Process evaluation survey

A process evaluation survey will be given to participants in the ACT group during the six-month follow-up. The survey will examine changes to their ideas of the ACT processes of smoking cessation [20] and their satisfaction with the ACT intervention in helping them to quit smoking.

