#### Biochemical measures

The level of exhaled carbon monoxide (CO) will be measured for all participants at baseline by means of a micro smokerlyser CO monitor. Urinary cotinine assays will be collected and the exhaled CO test will again be performed at the six-month follow-up session for self-reported quitters. Breath CO and cotinine have been found to be sensitive methods of determining smoking status [31] and exposure to tobacco smoke [32,33]. Participants with exhaled CO levels of 6 ppm or above [34] or a NicAlert test at level three or above according to the manufacturer will be considered current smokers.

The primary outcome will be self-reported seven-day point prevalence abstinence at the six-month follow up, meaning no smoking at all in the past seven days preceding the six-month follow-up assessment. Secondary outcomes will include: (i) validation of the self-report of not smoking obtained by the CO measurement and urinary cotinine; (ii) readiness to quit smoking; (iii) average number of cigarettes consumed daily in the past seven days; (iv) number of attempts to quit in the past month; (v) self-report of not smoking in the past seven days; and (vi) household smoking status in the past month.

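### The six-month session that blinded assessors are to conduct also carries an ACT-only telephone survey, and nothing keeps the two apart

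*Protocol article*

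**What the plan says.** Under Follow-up assessments, the protocol article describes the contacts as follows: "At three and six months, the participants will be re-contacted by telephone to complete the follow-up assessments assessing their smoking status". It then states the blind: "The assessments will be conducted by trained research assistants who are blind to the treatment condition". Next comes the step that depends on the interview: "Participants who self-report as quitters at the six-month follow-up interview will be invited to perform the CO test in the clinic". The paragraph closes with the survey: "Participants in the ACT group will also need to complete an evaluation survey through telephone at the six-month follow up session".

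The section Process evaluation survey repeats the arm and the timing: "A process evaluation survey will be given to participants in the ACT group during the six-month follow-up". Among its topics is "their satisfaction with the ACT intervention in helping them to quit smoking".

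Under Biochemical measures, "The primary outcome will be self-reported seven-day point prevalence abstinence at the six-month follow up". The biochemical check, "validation of the self-report of not smoking obtained by the CO measurement and urinary cotinine", is listed as a secondary outcome.

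**The concern.** A survey given to one arm reveals the arm to whoever has to decide whether to give it. Having the survey to give marks an ACT participant, and having none marks a control. The questions also identify the arm, because they concern ACT and satisfaction with it.

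This matters because the primary outcome is a self-report taken by telephone. Participants cannot be blinded to having received counselling, so the blinding of the assessor is the main protection when outcomes are collected. If the assessor knows the arm, that can colour how an ambiguous answer about smoking is probed and recorded, and how firmly a self-reported quitter is encouraged to attend for testing. The other six-month self-reports, such as daily cigarettes, quit attempts and readiness to quit, are exposed in the same way. Biochemical validation does not remove the problem: it is secondary, and at six months it is done only in people who have already reported quitting.

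**Working it through.** The document gives no figure for this point, so the check is mainly a comparison of its statements.

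1. **Who collects the outcome, and how.** Blinded research assistants, by telephone, at three and six months (Follow-up assessments).
2. **Who receives the survey, how and when.** The ACT arm only, by telephone, at the six-month session (Follow-up assessments). The Process evaluation survey section confirms the arm and the time.
3. **Is it the same session?** The Questionnaires section uses the same term, follow-up sessions, for the occasions on which the outcome questionnaire is completed. The Biochemical measures section also uses it for the six-month CO and cotinine tests. However, the CO test takes place in the clinic and the survey by telephone, so the survey does not belong to the clinic visit. The outcome call is the natural reading.
4. **Is there any separation?** No section assigns the survey to other staff, to a separate call, or to a point after the outcomes have been recorded.
5. **What follows.** An assessor who has to give the survey must be told who is in the ACT arm, before or during that session. If told beforehand, the assessor is unblinded when abstinence is recorded. If told only at the end, abstinence is safe, but the text does not provide for this.
6. **What does not follow.** The survey takes place only at six months, so it has no bearing on the three-month assessment.

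**Illustration only.** This shows how sensitive a trial of this size is to differential recording. It does not estimate the bias.
- Inputs from the Sample size section: 116 participants and a control quit rate of 7.4%.
- Assumptions: 1:1 allocation, giving 116/2 = 58 per arm; a true rate of 7.4% in both arms; a share m of ACT smokers wrongly recorded as abstinent; a simple two-sided 5% comparison of two proportions (normal approximation), not the mixed model that the article plans.
- Expected control quitters: 58 × 0.074 = 4.3.
- Recorded ACT rate: 0.074 + m × (1 − 0.074).

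| Assumed m | Recorded ACT rate | Chance of a significant result favouring ACT |
|---|---|---|
| 0 | 7.4% | 2.5% (nominal) |
| 2% | 9.3% | 5.5% |
| 5% | 12.0% | 13.1% |
| 10% | 16.7% | 33.3% |

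No value of m stands in the document, and nothing in it makes one row more likely than another.

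**The case against.** The best defence is that the article names an agent for the outcome assessments but none for the survey. The Randomization section shows that some staff know allocation, since a research assistant opens the envelopes. Such a person could give the survey and leave the blind intact. The paragraph also mentions the survey last, after the outcome assessment and the CO invitation. If the call follows that order and the assessor is prompted only at the end, abstinence is already recorded. Call scripts and staffing are details that a journal article commonly leaves to the full protocol. The primary question is a fixed yes-or-no item, so the assessor has limited discretion.

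Much of this stands. It rules out several stronger readings that a reader might infer:
- **That the two statements flatly contradict each other, or that every six-month assessment is unblinded.** Both can be true if someone else gives the survey or if it comes last.
- **That pursuit of non-responders is affected.** This would require the caller to know the arm before making contact. A survey given at the end of a completed call cannot do that.
- **That the bias can be sized at 1.7 percentage points per shifted classification.** That figure is 1/58. It would apply to any single misclassification with 58 per arm, and it says nothing about how many would occur.

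The appeal to condensation does not dispose of the point. The article does more than leave out a detail: it claims a blind and then places an arm-revealing task in the same session. Staff who followed the text as written could break the blind without departing from the protocol. Nor does it help that participants may disclose their arm anyway, because an avoidable leak in the procedure remains avoidable.

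**Conclusion.** The point holds in a conditional form. As written, the six-month procedure ties a survey that reveals the arm to the session in which blinded assessors collect the self-reported primary outcome and from which the CO invitation arises. On the natural reading this undermines the stated blind. The conclusion rests on two inferences that the article does not state: that the session means the outcome call, and that the outcome assessor gives the survey. For abstinence itself to be exposed, the assessor must also learn the arm before the answer is recorded.

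The size of any bias cannot be derived from the document. The illustration shows only that, with about four control quitters expected, a modest differential in recording would matter. The exposure is confined to six months, but that is where the primary outcome lies. The point is worth settling before the six-month calls; it does not show that the result would be invalid.

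**What to change.** Amend Follow-up assessments and Process evaluation survey to state that:

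- the blinded assessor has no access to allocation, records and locks all six-month outcomes, and makes the invitation to CO and cotinine testing identically in both arms;
- the ACT survey is given only afterwards, in a separate contact, by an existing team member who already knows allocation and did not deliver the counselling, or by post or online.

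This keeps the survey, which serves the acceptability aim under Treatment feasibility, and needs no new staff. The cost is one short extra contact per ACT participant, about 58 if allocation is 1:1, and possibly a slightly lower survey response because it no longer shares the outcome call.

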### Intervention

#### ACT

In addition to the self-help materials on smoking cessation given to the participants in both groups, the participants randomized to the ACT condition will be offered an initial individual face-to-face ACT session at the clinic and two telephone follow-up sessions at one week and one month following the initial session of ACT intervention. Each session will be around 15 to 20 minutes, for a total of approximately one hour over the three sessions. The sessions will be delivered by a counselor experienced in delivering ACT. The intervention will be based on a treatment protocol developed in this study, which is guided by previous ACT for smoking cessation protocols [19] and will incorporate all six core processes of ACT. The first session will mainly help the participants to: (1) accept their cravings and withdrawal symptoms as well as to develop skills for dealing with them without smoking, and (2) identify the values involved in quitting and develop a plan to stop smoking at the initial ACT intervention session. Subsequent sessions will include reinforcing the plan that was developed to quit smoking, supporting participants in continued actions to quit, guided by those identified values, and reinforcing the message on the value of quitting. ACT metaphors/exercises will be used throughout the three sessions. Table 1 provides a session-by-session outline of the intervention.

**Table 1 Tab1:** **Overview of the ACT sessions**

**Session**	**Format**	**Content**
1	Face-to-face	Clarifying values and barriers
		Identifying and clarifying the intention to cease smoking
		Recognizing “creative hopelessness”
		Two kids in the car metaphor
		The ACT in a nutshell metaphor
		Identifying internal triggers
		Appreciating that “control” is always unworkable
		Encourage participants to practice expansion (exercise 1)
		Dropping anchor (exercise 2)
		Introducing and cultivating mindfulness
		Practicing adaptive responses in the presence of internal triggers
2	Telephone	Brief update and bridge from the first face-to-face intervention
		Willingness as an alternative to control (emotional avoidance)
		Emphasize mindful responses with adaptive behaviors
3	Telephone	Brief update and bridge from the last telephone intervention
		Willingness as an alternative to control (emotional avoidance)
		Emphasize mindful responses with adaptive behaviors

#### Control and ACT

At the clinic, the participants will be provided with written self-help materials on smoking cessation (“Tips on quitting smoking”). The printed materials are available to the public and distributed by the Department of Health, HK. The materials describe strategies for tackling cravings and provide information on community resources for quitting smoking.

### Measures

#### Questionnaires

A structured questionnaire will be completed by participants at the baseline, three-month, and six-month follow-up sessions. Demographic data, including age, gender, educational level, current occupation, marital status, and number of people in the household will be recorded at baseline. The questionnaires include questions related to tobacco consumption, such as the number of cigarettes smoked per day, smoking behaviors, withdrawal symptoms, previous attempts to quit, and experiences. The participants’ readiness to quit smoking at different time points will also be recorded [25]. The questionnaires will also include the following scales:

#### Short Form-12 health survey (SF-12)

The SF-12 measures self-perceived general health status [26]. The results are expressed in terms of two meta-scores: the Physical Component Summary (PCS) and the Mental Component Summary (MCS). The PCS and MCS scores have a range of 0 to 100. They were designed to have a mean score of 50 and a standard deviation of 10 in a representative sample of the U.S. population. Thus, scores greater than 50 represent above average health status.

#### Fagerstrom Test for Nicotine Dependence (FTND)

The FTND [27] is a six-item scale that assesses the degree of nicotine dependence. Scores range from 0–10 and are categorized as very low (0–2), low (3–4), medium (5), high (6–7), or very high (8–10). The higher scores reflect higher levels of physiological dependence on nicotine. The FTND has adequate internal consistency and high test–retest reliability [27].

#### Acceptance and action questionnaire-II

The AAQ-II is derived from an earlier version of the AAQ [28], hereafter referred to as the AAQ-I. This is a 10-item self-report measure that assesses the degree of psychological inflexibility and experiential avoidance [29]. Some statements will be modified in relation to the smoking context. For example, the statement “I worry about being unable to control my worries and feelings” will be modified into “I worry about being unable to control my worries and feelings caused by smoking”. Response options will be 1 (strongly disagree), 2 (disagree), 3 (agree), and 4 (strongly agree). Higher total scores on the AAQ-II reflect greater psychological flexibility (and lower engagement in experiential avoidance). The AAQ-II has strong psychometric properties with a mean alpha coefficient of .84. The three-month and twelve-month test-retest reliability has been found to be .81 and .79, respectively [29].

#### Emotion Regulation Questionnaire (ERQ)

The ERQ consists of two subscales related to emotional control, namely cognitive reappraisal and expressive suppression [30]. Response options will be 1 (strongly disagree), 2 (disagree), 3 (agree), and 4 (strongly agree). The higher the total score a respondent obtains in a given subscale, the greater the use of that particular emotion-regulation strategy. Gross and John [30] found a test–retest reliability of 0.69 for both the reappraisal and suppression subscales, and determined that internal consistency of each subscale was acceptable.

#### Process evaluation survey

A process evaluation survey will be given to participants in the ACT group during the six-month follow-up. The survey will examine changes to their ideas of the ACT processes of smoking cessation [20] and their satisfaction with the ACT intervention in helping them to quit smoking.

#### Biochemical measures

The level of exhaled carbon monoxide (CO) will be measured for all participants at baseline by means of a micro smokerlyser CO monitor. Urinary cotinine assays will be collected and the exhaled CO test will again be performed at the six-month follow-up session for self-reported quitters. Breath CO and cotinine have been found to be sensitive methods of determining smoking status [31] and exposure to tobacco smoke [32,33]. Participants with exhaled CO levels of 6 ppm or above [34] or a NicAlert test at level three or above according to the manufacturer will be considered current smokers.

The primary outcome will be self-reported seven-day point prevalence abstinence at the six-month follow up, meaning no smoking at all in the past seven days preceding the six-month follow-up assessment. Secondary outcomes will include: (i) validation of the self-report of not smoking obtained by the CO measurement and urinary cotinine; (ii) readiness to quit smoking; (iii) average number of cigarettes consumed daily in the past seven days; (iv) number of attempts to quit in the past month; (v) self-report of not smoking in the past seven days; and (vi) household smoking status in the past month.

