**Study design.**

### Participants

#### Selection criteria

Individuals who meet the inclusion criteria will be recruited. The criteria are: (1) aged 18 years or above; (2) have smoke at least one cigarette per day in the past 30 days; (3) not currently undergoing any other smoking cessation program; (4) able to communicate in Cantonese; (5) a Hong Kong resident; (6) currently residing in Hong Kong and expecting to continue for the next six months; and (7) have access to a telephone.

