## Discussion

While research has found that ACT is effective for smoking cessation, no controlled trial studies of telephone-based ACT for smoking cessation has been conducted to date. To the best of our knowledge, this will be the first RCT examining the effectiveness of telephone-based ACT for smoking cessation. It is also the first study that examines the feasibility of the use of telephone-based ACT among a Chinese population.

The results of this study will provide clinicians with the necessary information to develop strategies to help smokers to stop smoking by using a less intense intervention at a time convenient to them. If found to be effective, this therapy can potentially be practiced by a wider range of clinicians than other therapies, given that it is much briefer and readily manualized than existing psychological treatments. It also has the potential to serve as an alternative useful tool for those who do not benefit from other commonly used treatments (e.g. Nicotine-Replacement Therapy, Cognitive Behavioral Therapy). In addition, this proactive recruitment approach may reach service users who might not otherwise be reached using traditional reactive approaches (e.g. Quitline, smoking cessation clinic, etc.). Information on the feasibility of this innovative smoking cessation intervention will provide further insight into its development. If this intervention program is well received by smokers and effective in helping those who smoke to quit, it could be offered to a larger population in Hong Kong or elsewhere at a low cost. It is believed that this telephone-based ACT will, in particular, acceptable to people in HK, as it can save time and allow them time for competing commitments. One anticipated difficulty for the study is subject requirement. However, the plan to establish multiple venues for recruitment with the inclusion of six primary care centers and a longer recruitment period should go some way towards ensuring an adequate participant pool.

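### The either-test verification rule has no exception for non-smoked nicotine, so a true abstainer using nicotine replacement at six months is counted as a smoker in verified abstinence

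*Protocol article*

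**What the plan says.** All references are to the protocol article.

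- **Rule (Biochemical measures).** Those with a CO reading of at least 6 ppm or "a NicAlert test at level three or above according to the manufacturer will be considered current smokers". The two tests are joined by "or", and no exception is stated.
- **Who is tested (same section).** At six months, "the exhaled CO test will again be performed at the six-month follow-up session for self-reported quitters"; urinary cotinine is collected as well. The rule can therefore only turn a self-reported quitter into a smoker.
- **Outcomes (same section).** "The primary outcome will be self-reported seven-day point prevalence abstinence at the six-month follow up", explained there as no smoking at all in the preceding seven days. Secondary outcome (i) is "validation of the self-report of not smoking obtained by the CO measurement and urinary cotinine".
- **Other cessation help.** Under Selection criteria, participants must be "not currently undergoing any other smoking cessation program". This applies at entry and concerns programs. Nothing shown bars nicotine replacement during follow-up. Under Control and ACT, the printed materials given to both arms "provide information on community resources for quitting smoking". The Discussion sees the intervention as an alternative for "those who do not benefit from other commonly used treatments (e.g. Nicotine-Replacement Therapy, Cognitive Behavioral Therapy").

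**The concern.** The outcome is about smoking, but one of the two tests measures nicotine. Cotinine is formed from nicotine whatever its source, so a positive strip does not separate a smoker from someone who has stopped smoking and wears a patch or chews nicotine gum. CO can separate them, because it comes from burnt tobacco. Under an either-test rule the positive strip settles the matter and the CO reading is ignored. For this group the rule contradicts the outcome that it is meant to verify.

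The article states cut-offs and how they are combined, so the problem lies in what the rule says and not in a detail left out.

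At stake is verified abstinence, the only objective check on a self-reported primary outcome in a trial whose participants know whether they received counseling. Few quitters are expected, so that check is sensitive to one or two misclassified people.

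**Working it through.** **1. Classification under the rule for a self-reported quitter**

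| True state at six months | CO | Cotinine strip | Class under the rule | Correct? |
|---|---|---|---|---|
| Not smoking, no nicotine | below 6 ppm | below level 3 | abstinent | yes |
| Smoking | 6 ppm or above, or missed | level 3 or above | smoker | yes |
| Not smoking, uses nicotine replacement | below 6 ppm | level 3 or above | smoker | no |

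Only the third row fails. It assumes enough nicotine intake to reach level 3.

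**2. Inputs for the size**

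- Sample size 116 and control quit rate 7.4% (Sample size). I assume equal allocation: 116 / 2 = 58 per arm.
- ACT quit rate: not stated. The pooled effect size of 0.475 (Sample size) can be converted to a proportion in more than one way, so I use two.
  - Logit: logit(p) = ln(0.074/0.926) + 0.475 × π/√3 = −2.527 + 0.862 = −1.665, so p = 15.9%.
  - Cohen's h: p = sin²(arcsin √0.074 + 0.475/2) = 24.1%.
- f, the share of true abstainers using non-smoked nicotine at six months: not in the document. Assumed range 10% to 30%.

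Expected true quitters: control 58 × 0.074 = 4.3; ACT 58 × 0.159 = 9.2 or 58 × 0.241 = 14.0.

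The article gives no figure for verified abstinence or for nicotine replacement use, so there is no stated result to reproduce.

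**3. Effect on the verified comparison**

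Verified rate = true rate × (1 − f). Expected number misclassified = 58 × true rate × f.

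| ACT true rate | f control / f ACT | Verified control / ACT | Difference (points) | Risk ratio | Misclassified control / ACT |
|---|---|---|---|---|---|
| 24.1% | 0 / 0 | 7.4% / 24.1% | 16.7 | 3.26 | 0 / 0 |
| 24.1% | 10% / 10% | 6.7% / 21.7% | 15.0 | 3.26 | 0.43 / 1.40 |
| 24.1% | 20% / 20% | 5.9% / 19.3% | 13.4 | 3.26 | 0.86 / 2.80 |
| 24.1% | 30% / 30% | 5.2% / 16.9% | 11.7 | 3.26 | 1.29 / 4.19 |
| 24.1% | 30% / 10% | 5.2% / 21.7% | 16.5 | 4.19 | 1.29 / 1.40 |
| 24.1% | 10% / 30% | 6.7% / 16.9% | 10.2 | 2.53 | 0.43 / 4.19 |
| 15.9% | 0 / 0 | 7.4% / 15.9% | 8.5 | 2.15 | 0 / 0 |
| 15.9% | 20% / 20% | 5.9% / 12.7% | 6.8 | 2.15 | 0.86 / 1.84 |
| 15.9% | 30% / 10% | 5.2% / 14.3% | 9.1 | 2.76 | 1.29 / 0.92 |
| 15.9% | 10% / 30% | 6.7% / 11.1% | 4.5 | 1.67 | 0.43 / 2.77 |

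With equal shares the factor (1 − f) cancels from the ratio and scales down the difference. With unequal shares either measure can move either way. At 24.1%, more controls than ACT participants are misclassified only if the control share exceeds 24.1/7.4 = 3.3 times the ACT share.

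**4. Sensitivity to single people (assumed counts, 58 per arm, Pearson chi-square without correction)**

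- 10 vs 4: 10.3 points, p = 0.087.
- One ACT abstainer reclassified, 9 vs 4: 8.6 points, p = 0.14.
- One reclassified in each arm, 9 vs 3: 10.3 points, p = 0.067.
- One ACT and two controls reclassified, 9 vs 2: 12.1 points, p = 0.027 (Fisher's exact p = 0.053).

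These counts show fragility. They predict nothing.

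**The case against.** **Reach.** The primary outcome is self-report, and the article does not say that a positive strip overrides it. A reader might infer that the main result is distorted, but the text does not support that. This objection stands: only secondary outcome (i) is affected.

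**Direction.** A reader might infer that controls, who have no counselor, will turn more to outside aids, so that the rule exaggerates the effect of ACT. The document does not support this. Both arms receive the same printed materials, and no use by arm is given. One could equally argue that participants who make a quit plan with a counselor seek more aids. The 9 vs 2 example needs 2 of 4 control abstainers (50%) but only 1 of 10 in the ACT arm (10%) to be using nicotine replacement, and it stays above 0.05 by Fisher's exact test. Equal shares shrink the absolute difference. This objection also stands, and no direction is claimed.

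**Frequency.** The materials are described only as covering community resources, without naming nicotine replacement, and the Discussion does not say that participants will use it. Use at six months could be nil. That is fair as to size. It does not make the rule right for those who do use it, and nothing shown excludes them.

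**Condensed article.** The full questionnaire may record nicotine products, so I do not claim that this information goes uncollected. But the classification rule is printed without exception, and recording use changes nothing unless the rule refers to it.

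**Deliberate strictness.** Requiring both tests to be negative catches smokers whom CO alone misses. That is a good reason to keep the rule for participants who report no other nicotine source, but not for those whose positive strip has another explanation.

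**Conclusion.** The point holds as a flaw in a stated rule for a secondary outcome. A participant who does not smoke but takes nicotine in another form at six months is classed as a smoker, against the protocol's own definition of abstinence. This rests on general pharmacology (cotinine follows nicotine from any source) and on the absence, in the text shown, of any bar to such products after entry.

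The size is unknown. Under the assumed shares of 10% to 30%, about 0.4 to 1.3 controls and 0.9 to 4.2 ACT participants would be misclassified. With equal shares of 30%, a true difference of 16.7 points would appear as 11.7, with the risk ratio still 3.26. The direction under unequal shares cannot be settled from the document. With about 4 control quitters expected, even one or two reclassifications would matter to the verified comparison.

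**What to change.** In Biochemical measures, make the rule depend on reported nicotine use:

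1. At the six-month follow-up, ask self-reported quitters in both arms, with the same wording, whether they currently use any nicotine-containing product and which.
2. Classify those who report non-smoked nicotine use by exhaled CO alone, at the cut-off already stated.
3. Keep the CO-or-cotinine rule for all others.
4. Report the number in each arm classified by CO alone.
5. Give verified abstinence under the either-test rule for all participants as a sensitivity analysis.

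The cost is one question at an interview already planned, a sentence or two in the outcome definition and one extra analysis. CO is already to be measured in these participants, so no new test is needed. The downside is that CO alone is less sensitive to smoking, so a smoker who reports nicotine replacement could be missed. The sensitivity analysis and the counts per arm show how much depends on this.

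### The primary outcome rests on self-report alone, so a six-month quitter whose planned CO or cotinine test is positive still counts as a success

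*Protocol article*

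**What the plan says.** All references are to the protocol article.

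- **Primary outcome** (Biochemical measures): "The primary outcome will be self-reported seven-day point prevalence abstinence at the six-month follow up". Abstinence is defined as having smoked nothing during the week before that assessment. No biochemical condition is attached.
- **Who is tested at six months** (Biochemical measures): urinary cotinine is collected, and "the exhaled CO test will again be performed at the six-month follow-up session for self-reported quitters".
- **What a positive test means** (Biochemical measures): participants with exhaled CO of 6 ppm or more, "or a NicAlert test at level three or above according to the manufacturer will be considered current smokers".
- **Where verification enters** (Biochemical measures): secondary outcome (i) is "validation of the self-report of not smoking obtained by the CO measurement and urinary cotinine". Secondary outcome (v) is the self-report again, which at six months repeats the primary.
- **How the test is arranged** (Follow-up assessments): "Participants who self-report as quitters at the six-month follow-up interview will be invited to perform the CO test in the clinic". Cotinine is not mentioned there. The same section says that the research assistants who do the follow-up are blind to treatment.
- **What each arm receives** (Intervention, ACT; Control and ACT): both arms get printed self-help material. The ACT arm also has one face-to-face and two telephone counselling sessions.

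**The concern.** At six months the tests are given only to people whom the primary outcome already counts as abstinent. The only thing a test can do at that point is support or overturn a primary success, yet the primary outcome ignores the result. A known false success stays in the numerator.

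This matters because the primary outcome is the participant's own statement, and participants know their arm. ACT participants have worked with a counsellor on their values and on a plan to stop smoking; controls have had a leaflet. If continuing smokers in the ACT arm are more inclined to say that they have quit, the apparent ACT rate rises without any true effect. In a trial of 116 people with a low quit rate, a few such reports are enough to matter. One participant is 1/58 = 1.7 percentage points of an arm, and the expected number of true quitters per arm at 7.4% is 58 × 0.074 = 4.3.

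**Working it through.** The plan gives no figure for over-reporting, so there is nothing of its own to reproduce here. The calculation shows only how sensitive the primary comparison is.

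**Inputs**
- Control quit rate 7.4% and total sample 116 (Sample size).
- 58 per arm: an assumption of 1:1 allocation, since the article does not state the ratio.
- Two-sided 5% level: the article states 5% without sidedness.
- Over-reporting shares f_A (ACT) and f_C (control) among continuing smokers: assumptions, shown as a range.
- True quit rate 7.4% in both arms, that is, no treatment effect.

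**Formulae**
- Apparent rates: p_A = 0.074 + 0.926 × f_A and p_C = 0.074 + 0.926 × f_C.
- Test for x_A and x_C reported quitters: z = [(x_A − x_C)/58] / √[p̄(1 − p̄) × 2/58], with p̄ = (x_A + x_C)/116 and no continuity correction.
- Chance of a significant result favouring ACT: the sum of Bin(x_A; 58, p_A) × Bin(x_C; 58, p_C) over all pairs with z > 1.96.

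**Example.** With f_A = 0.05 and f_C = 0, p_A = 0.074 + 0.926 × 0.05 = 0.120. The expected number of false reports is 58 × 0.926 × 0.05 = 2.7 people.

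| f_A | f_C | Apparent ACT | Apparent control | Chance of significance favouring ACT |
|---|---|---|---|---|
| 0 | 0 | 7.4% | 7.4% | 2.4% |
| 2% | 0 | 9.3% | 7.4% | 5.4% |
| 5% | 0 | 12.0% | 7.4% | 13.0% |
| 10% | 0 | 16.7% | 7.4% | 33.6% |
| 5% | 3% | 12.0% | 10.2% | 5.0% |
| 5% | 5% | 12.0% | 12.0% | 2.5% |

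**How large these shares are.** Among ACT participants who report abstinence, the false share is 0.926 × f_A / p_A: 0.0185/0.0925 = 20% at f_A = 2%, 0.0463/0.1203 = 38% at 5%, and 0.0926/0.1666 = 56% at 10%.

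**Choice of test.** With Fisher's exact test in the same enumeration, 5% in ACT only gives 6.9% rather than 13.0%. That test is conservative at these rates: with no over-reporting it gives 0.8%. The article's stated analysis is a mixed model for repeated measures, so none of these figures is the plan's own error rate.

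**The case against.** **Two endpoints, not a conflict.** A reader might infer that the section contradicts itself, because one person can be a quitter and a current smoker at once. The text does not force that reading. Self-report is named as primary and validation as secondary (i), so the smoker rule can be taken to define the secondary outcome only. This stands: the point concerns the choice of primary definition. The article does not, however, say which status governs when report and test disagree.

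**Verification is already planned, in a small feasibility trial.** This is true, and the primary is not the only outcome that bears on efficacy, since the Statistical analysis section speaks of outcome measures in the plural. But the primary outcome is where false successes do most harm, and the data to remove some of them will be at hand.

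**Assessors are blind.** A reader might call the trial simply unblinded. The article does not support that, because follow-up is by blind research assistants and not by the counsellor. Their blinding does not correct what a participant chooses to say.

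**Differential over-reporting is inferred.** This stands. No document gives a rate in either arm. The 13% and 34% figures assume none among controls, and they require 38% and 56% of ACT self-reported quitters to be false. With similar over-reporting in both arms the inflation largely or wholly disappears.

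**Nicotine replacement.** A reader might infer that the cotinine rule mislabels abstainers who use nicotine replacement, since the leaflet is said to "provide information on community resources for quitting smoking". The article does not say that these resources supply nicotine replacement, neither arm includes it, and as written the rule does not enter the primary outcome. The point does not rest on this.

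**Conclusion.** The point holds as a weakness in the primary definition. A self-report contradicted by the trial's own test remains a primary success, in a trial whose participants know their arm.

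The size is uncertain. Under no true effect, the chance of a significant result favouring ACT runs from about 2.5% (equal over-reporting) through about 5% (2% in ACT only, or 5% against 3%) to 13% and 34% (5% and 10% in ACT only). These figures rest on 58 per arm, a 7.4% true rate in both arms, an uncorrected z test and assumed over-reporting shares. They show sensitivity and do not predict bias in this trial. Differential over-reporting is possible here; the documents do not establish it.

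**What to change.** 1. Define primary abstinence as self-reported seven-day abstinence at six months, with any positive test under the plan's own CO or NicAlert rule counted as smoking.
2. Report two further rates as secondary or sensitivity analyses: self-report only, which secondary outcome (v) already supplies at six months, and strictly verified, with a self-reported quitter who has no test counted as smoking.
3. Report test attendance by arm.
4. Align the Follow-up assessments section, which mentions only CO, with Biochemical measures, which adds cotinine.

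**Cost.** The change is to wording, as the tests are already planned. Quit rates will be slightly lower. A false reporter who does not come to the clinic cannot be contradicted, and attendance may itself differ by arm, so the change reduces the bias without removing it. The strictly verified rate and the attendance figures let a reader judge what remains.
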